### 2.3. Data Collection

#### 2.3.1. Outcomes

The primary outcomes will be the changes in PTSD, anxiety, and depression symptoms, and levels of social support from baseline to postintervention. Secondary outcomes will include participant satisfaction and insights derived from the qualitative data.

Participants will complete a battery of self-report questionnaires at three time points: baseline (T0), postintervention (T1), and at a 1-month follow-up. The assessment includes the International Trauma Questionnaire (ITQ), Generalized Anxiety Disorder 7-item scale (GAD-7), PHQ-9, Health Questionnaire (EQ-5D-5L), the Oslo Social Support Scale (OSSS-3), and 5-Question Stigma Indicator—Affected People.

In addition to the quantitative assessments, a qualitative component will be included postintervention. Semistructured interviews will be conducted with participants from both the intervention and control groups to explore their experiences and views regarding the TSR intervention and standard care, respectively. This qualitative data will provide deeper insights into the feasibility, acceptability, and effectiveness of the intervention.

The sociodemographic questionnaire will collect essential background information about the participants, including age, gender, marital status, education level, employment status, and duration of leprosy diagnosis. These data are crucial for understanding the context in which participants live and how various demographic factors might influence their mental health outcomes. The sociodemographic information will help in identifying potential correlations between participants' backgrounds and their responses to the intervention, ensuring that any observed effects are appropriately contextualized.

The quantitative data will be analyzed using intention-to-treat principles, with comparisons between the intervention and control groups, whereas the qualitative data will be analyzed using the reflexive thematic analysis [32–35].

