The current project will test TSR's potential effectiveness in reducing symptoms of PTSD, anxiety, and depression. Specifically, it will evaluate the feasibility of recruiting individuals with leprosy for the TSR intervention, assessing its acceptability through various parameters such as recruitment rates, participant engagement, session attendance, and dropout rates. Qualitative interviews will further explore these aspects. The study will also define appropriate primary and secondary outcomes for assessing the intervention's effect in a full-scale trial. Data from this study will inform the design of a future multisite definitive clinical trial, including optimizing the design and planning the sample size. By focusing on this underserved population, the study aims to fill a critical gap in the literature and provide a foundation for future research on the effectiveness of mental health interventions for individuals with leprosy. The findings will have significant implications for public health strategies in similar contexts and could lead to the development of more comprehensive care models that address both the physical and psychological needs of individuals affected by leprosy.

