### 2.1. Study Design

This randomized controlled trial (RCT) with a qualitative component is designed to assess the effectiveness of the TSR intervention for individuals affected by leprosy in Addis Ababa, Ethiopia.

Methodological features of this feasibility RCT will minimize the possible bias in the intervention group. These features include allocation concealment (that will be ensured by randomization to be performed by an independent, off-site statistician), blinding (study statistician and the research team carrying out follow-up assessments will be masked to treatment allocation), use of intention-to-treat analysis, and the use of primary versus secondary endpoints.

The study will involve two arms: an intervention group receiving the TSR intervention and a waitlist control group. Participants will undergo individual randomization conducted by an off-site statistician. A total of 100 participants will be randomized in a 1:1 ratio into either the TSR intervention group (*n* = 50) or the waitlist control group (*n* = 50). Randomization will occur after baseline assessments using a computer-generated sequence to ensure allocation concealment.

As this study first of its kind and aims to demonstrate a trend in favor of the intervention and the recruitment and retention of participants into the study, the sample size was informed by community consultation and trial guidelines [20–25] to ensure a sample that allows for the estimation of recruitment and retention parameters, as well as potential effectiveness.

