The present trial is designed to evaluate the feasibility and acceptability of the TSR for individuals with lived experience of leprosy in Addis Ababa, Ethiopia. The TSR aims to reduce symptoms of PTSD, anxiety, and depression while enhancing social support and overall mental health. This trial will assess whether the TSR is a viable and effective intervention for this population, and whether it can be implemented in a culturally sensitive manner that addresses the unique challenges faced by individuals with leprosy.

This trial has several limitations. First, challenges related to stigma and social isolation might pose difficulties in recruitment and participant engagement, potentially leading to a biased sample. Second, the relatively small sample size may limit the generalizability of the results. Third, the absence of a long-term follow-up may limit the understanding of the sustained effects of the intervention. Despite these limitations, this trial will provide valuable insights into the feasibility of implementing culturally adapted mental health interventions for individuals affected by leprosy. The inclusion of qualitative interviews will further enhance our understanding of the participants' experiences and inform the design of future RCTs aimed at evaluating the effectiveness of the TSR. Most importantly, the strength of the current study is in its potential to ensure there is a sustainable, stigma-friendly response beyond the project as it includes not only professionals but also nonspecialist peer supporters with lived experience in TSR.

In conclusion, this trial represents an important step toward improving mental health care for individuals affected by leprosy. By evaluating the feasibility of the TSR in a culturally sensitive context, this study will contribute valuable knowledge to the field and lay the groundwork for future research on effective mental health interventions for marginalized populations and/or for people affected by NTD. The findings from this trial are expected to provide critical insights into how culturally adapted interventions can be used to support the psychological well-being of individuals living with leprosy, ultimately paving the way for future RCTs.

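### The outcomes ranked primary are effectiveness changes, while the trial's stated feasibility purpose, only sample-size figure and Stop-Go rule rest on recruitment and retention, which have no rank

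*Protocol article*

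**What the plan says.** **Ranking.** Section 2.3.1 of the protocol article gives the primary tier: "The primary outcomes will be the changes in PTSD, anxiety, and depression symptoms, and levels of social support from baseline to postintervention". The next sentence gives the other tier: "Secondary outcomes will include participant satisfaction and insights derived from the qualitative data".

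**Purpose.** Section 2.1 says the trial is to assess effectiveness, then calls it a feasibility RCT and says that it "aims to demonstrate a trend in favor of the intervention". The Discussion (section 3) says: "The present trial is designed to evaluate the feasibility and acceptability of the TSR". The Introduction adds, with a later full-scale trial in view: "The study will also define appropriate primary and secondary outcomes".

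**Sample size.** Section 2.1: "A total of 100 participants will be randomized in a 1:1 ratio into either the TSR intervention group", with 50 planned per arm. The number was informed by consultation and guidelines "to ensure a sample that allows for the estimation of recruitment and retention parameters, as well as potential effectiveness". The only figure attached to it is in section 2.4: ±8% accuracy for recruitment and retention rates with 100 participants.

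**Decision rule.** The Stop-Go criterion in section 2.4 uses retention for its upper two bands (70% or higher; 50% to 70%) and recruitment for its lowest (below 50%). No clinical scale enters it.

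**Where feasibility sits.** Section 2.3.1.8 describes recruitment, attrition and attendance as indicators to be monitored. It assigns them no primary or secondary rank.

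**Schedule.** Section 2.3.1 lists all the questionnaires, OSSS-3 and the stigma indicator included, at three time points. Section 2.3.1.5 and Table 1 place the OSSS-3 at baseline only. Section 2.3.1.6 and Table 1 place the stigma indicator before the intervention only.

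**The concern.** The primary outcome should be the quantity the trial is built to answer. Here the explicit ranking points to clinical benefit, while the stated feasibility purpose, the only precision figure and the only decision rule point to recruitment and retention. The trial is also meant to help choose the outcomes of a later trial, yet it already ranks four of the candidates as primary.

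Section 2.1 presents the separation of primary from secondary endpoints as a protection against bias. That protection is weak when the ranking leaves out the quantities on which the go decision depends.

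If the text is followed as written, the headline result is an effectiveness result from a sample with no stated effect size, SD or power for one. A wide interval around a moderate true benefit could be read as failure, and a favourable estimate could be read as proof. The question with a stated precision and a decision rule would be reported below the headline.

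**Working it through.** **1. The plan's own figure.** Inputs from section 2.4: n = 100, 95% confidence, ±8%. The rate p is not given. Half-width = 1.96 × √(p(1 − p)/100):

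| p | Half-width (percentage points) |
|---|---|
| 0.80 | 7.8 |
| 0.79 | 8.0 |
| 0.70 | 9.0 |
| 0.50 | 9.8 |

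The ±8% therefore reproduces at a rate of about 79% to 80%. At the Stop-Go thresholds of 70% and 50% it is about ±9 and ±10. For retention, the figure is a genuine precision statement. It does not carry over directly to recruitment, because section 2.3.1.8 defines that rate among eligible people referred, not among the 100 randomized.

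**2. The corresponding figure for the four primary outcomes.** There is none: no effect size, SD, significance level or power appears in the article. To show what the sample could support, assume a two-sided 5% level, 80% power and an unadjusted two-sample t-test. In the normal approximation, d = (1.960 + 0.842) × √(2/n per arm); the t-test value is slightly larger.

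- 50 per arm (full retention): 2.802 × √(2/50) = 0.56; t-test 0.57.
- 35 per arm (50 × 0.70, the go threshold): 2.802 × √(2/35) = 0.67; t-test 0.68.

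**3. Allowing for baseline.** Section 2.4 plans to account for baseline severity. If baseline and outcome correlate at r, the detectable difference shrinks by √(1 − r²). The article gives no r, so a range is assumed:

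| Assumed r | 50 per arm | 35 per arm |
|---|---|---|
| 0 (unadjusted) | 0.57 | 0.68 |
| 0.5 (factor 0.866) | 0.49 | 0.59 |
| 0.7 (factor 0.714) | 0.40 | 0.49 |

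**4. Elements side by side.**

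| Element | Recruitment and retention | Clinical changes |
|---|---|---|
| Stated purpose | Feasibility RCT (2.1); feasibility and acceptability (3) | Effectiveness (2.1) |
| Sample-size basis | Named, with ±8% | Named as potential effectiveness, no figure |
| Stop-Go rule | Entire rule | None |
| Outcome rank | None | Primary |

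**5. Can all four changes be computed?** A change from baseline needs a post-intervention value. On the schedule in section 2.3.1.5 and Table 1 the OSSS-3 has none, so the social support change could not be estimated. On the schedule in section 2.3.1 it could. The passages disagree.

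**The case against.** The defence has several good points, and they limit how far this goes.

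- **Potential effectiveness is part of the sample-size sentence.** This stands. It would be wrong to say that the sample was justified by recruitment and retention alone. What can be said is that no number supports the effectiveness part.
- **Feasibility measures are not missing.** This also stands. They have their own subsection under the Outcomes heading, they are aims in the Introduction, and section 2.4 promises confidence intervals for the rates. The secondary list need not be exhaustive. They are unranked, not absent.
- **Baseline adjustment improves sensitivity.** It does, hence the range shown above. An unadjusted figure on its own would overstate the problem.

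Two stronger readings are tempting, and the documents do not support them.

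- **Inflated false-positive risk.** A reader might infer that four primary outcomes without a multiplicity rule let any one significant result count as success, and quote 1 − 0.95⁴ = 18.5%. That needs a 5% level for each outcome, independence, four testable outcomes and a rule that any one suffices. The article states no significance level and no success rule, calls the trial exploratory, and may leave multiplicity to an analysis plan that is not shown. On the Table 1 schedule only three of the changes could be tested.
- **A conclusion fixed in advance.** A reader might infer this from the aim of showing a favourable trend. The wording is poor, but the Introduction speaks of testing potential effectiveness, and the interviews ask what did not work and invite people who dropped out.

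None of this answers the central point. The ranking is an explicit sentence, so condensation into an article does not explain it, and an analysis plan would not normally re-rank a protocol's primary outcomes.

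**Conclusion.** The concern holds as a mismatch between the outcome ranking and the rest of the design. Four effectiveness changes are primary in a trial whose feasibility purpose, only precision figure and whole decision rule concern other quantities, and those quantities have no rank. This rests on the text alone.

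The size is illustrative. At an assumed two-sided 5% level and 80% power, the detectable d at 50 per arm runs from about 0.57 unadjusted to about 0.40 with an assumed baseline correlation of 0.7. At 35 per arm it runs from about 0.68 to 0.49. A small or modest benefit could easily be missed, though the article gives no expected effect against which to judge this. No claim is made about family-wise error. The change should be made, and it alters what the trial may conclude.

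**What to change.** 1. **Section 2.3.1, primary tier.** Make recruitment and retention rates the primary outcomes, with TFA acceptability if wanted, so that they match the Stop-Go rule.
2. **Section 2.3.1, secondary tier.** Make ITQ, GAD-7, PHQ-9 and EQ-5D-5L secondary exploratory outcomes, reported as baseline-adjusted between-arm differences with 95% confidence intervals and no claim of effectiveness.
3. **Section 2.1.** Replace the aim of showing a favourable trend with estimating the between-arm difference, and bring the opening statement about assessing effectiveness into line with the feasibility purpose in the Discussion.
4. **OSSS-3 and stigma indicator.** Before placing either in a tier, reconcile section 2.3.1 (three time points) with sections 2.3.1.5, 2.3.1.6 and Table 1 (before the intervention only). Without a post-intervention value neither can yield a change or an effect estimate.

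**Cost.** Items 1 to 3 need no change to the sample size or to the recruitment procedures. The sponsor must formally amend the stated primary outcomes, which is more than an edit of wording, and gives up a headline effectiveness claim. Item 4 adds assessments only if the three-time-point schedule is the one kept.

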##### 2.3.1.1. ITQ-Administered Pre- and Posttreatment

The ITQ is a self-report measure designed to assess symptoms of PTSD and complex PTSD (CPTSD) as defined by the ICD-11 [36]. This questionnaire focuses on core PTSD symptoms such as re-experiencing, avoidance, and a sense of current threat, as well as disturbances in self-organization, including affective dysregulation, negative self-concept, and difficulties in relationships. The tool has a good level or factor structure in Ethiopia [37].

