##### 2.3.1.2. GAD-7-Administered Pre- and Posttreatment

The GAD-7 is a widely used self-report tool for assessing the severity of generalized anxiety symptoms. Participants will complete the GAD-7 at baseline and postintervention to evaluate changes in anxiety levels resulting from the TSR intervention. The tool has a good level or factor structure in Ethiopia [38].

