##### 2.3.1.3. PHQ-9-Administered Pre -and Posttreatment

The PHQ-9 is a validated tool used to measure the severity of depressive symptoms. This self-report measure will be administered at both baseline and postintervention to assess changes in depression levels among participants. The tool has a good level or factor structure in Ethiopia [39].

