## Figures and Tables

**Table 1 tab1:** Design of the planned intervention.

	Study period			
	Enrollment	Baseline assessment	The intervention	Postintervention assessment
	−*t*1	*t*0	4 sessions	*t*1
Enrollment:				
Eligibility screen	X			
Informed consent	X			
Intervention: TSR				
Assessments:				
Sociodemographic Questionnaire		X		
International Trauma Questionnaire (ITQ)		X		X
Generalized anxiety disorder 7-item (GAD-7)		X		X
Patient Health Questionnaire-9 (PHQ-9)		X		X
Health Questionnaire (EQ-5D-5L)		X		X
Oslo Social Support Scale (OSSS-3)		X		
5-Question stigma indicator—affected people		X		
TFA Acceptability Questionnaire				X
Qualitative interview				X

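### The 1-month follow-up is promised in one sentence, but neither Table 1 nor any scale's own section schedules it, so the visit and the time point for Stop-Go retention are unsettled

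*Protocol article*

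**What the plan says.** Section 2.3.1 (Outcomes) states that the battery is completed "at three time points: baseline (T0), postintervention (T1), and at a 1-month follow-up". It lists the ITQ, GAD-7, PHQ-9, EQ-5D-5L, OSSS-3 and the 5-Question Stigma Indicator. The same section fixes the primary window: "The primary outcomes will be the changes in PTSD, anxiety, and depression symptoms, and levels of social support from baseline to postintervention".

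The later sections differ:
- The ITQ section is headed "ITQ-Administered Pre- and Posttreatment".
- For the GAD-7: "Participants will complete the GAD-7 at baseline and postintervention".
- The PHQ-9 "will be administered at both baseline and postintervention to assess changes in depression levels among participants".
- The EQ-5D-5L section also gives baseline and postintervention.
- The OSSS-3 section gives baseline only, and the stigma section gives a measurement before the intervention only.

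The last column of Table 1 is "Postintervention assessment", labelled t1. Section 2.4 plans descriptive statistics for baseline and postintervention. It does not say which time points enter the repeated measures analysis, nor at which visit Stop-Go retention is counted. Section 2.1 describes the arms as "an intervention group receiving the TSR intervention and a waitlist control group".

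**The concern.** An article may leave detail to the full protocol, but here it gives two assessment schedules that cannot both be followed. A site working from Table 1 would close data collection at t1. A site working from the opening of section 2.3.1 would call participants back a month later.

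Two things are at stake. The first is whether any 1-month data exist for a trial meant to inform a definitive one. The second is the progression decision. Section 2.4 separates proceeding from remedial action at 70% retention, and retention at T1 can differ from retention a month later.

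**Working it through.** No sample size or power figure bears on this point, so the check sets the stated assessment times side by side.

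| Scale | Opening of 2.3.1 | Scale's own section | Table 1 |
|---|---|---|---|
| ITQ | T0, T1, 1 month | pre, post | t0, t1 |
| GAD-7 | T0, T1, 1 month | pre, post | t0, t1 |
| PHQ-9 | T0, T1, 1 month | pre, post | t0, t1 |
| EQ-5D-5L | T0, T1, 1 month | pre, post | t0, t1 |
| OSSS-3 | T0, T1, 1 month | baseline | t0 |
| Stigma indicator | T0, T1, 1 month | before intervention | t0 |

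**Count of entries.** The opening statement implies 6 × 3 = 18. Table 1 has 4 × 2 + 2 × 1 = 10. The difference is 8: 6 entries at one month (every scale) and 2 at T1 (OSSS-3 and stigma indicator). Scales scheduled at one month outside the opening statement: 0 of 6.

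**Data at stake.** With 100 randomised (section 2.1), three visits give at most 3 × 100 = 300 participant assessments. The unscheduled visit is up to 100 of these, or one third, if nobody is lost.

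**Other mentions of follow-up.** Section 2.1 says that staff doing follow-up assessments are masked, without naming a time. The Discussion lists the lack of long-term follow-up as a limitation, which fits either schedule. Neither settles the matter.

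**Stop-Go.** Assume that retention is counted out of the 100 randomised; section 2.4 does not give the denominator. Retention of 70 or more means proceed. If R participants are retained at T1, the result changes from proceed to remedial action once R − 69 more are lost by one month:

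| Retained at T1 (assumed) | Further losses that change the result |
|---|---|
| 70 | 1 |
| 75 | 6 |
| 80 | 11 |
| 90 | 21 |

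The choice of visit can therefore decide the outcome when T1 retention is a little above 70%. It is unlikely to matter when T1 retention is high.

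**The case against.** The strongest reply is that the conflict does not reach the primary comparison. Section 2.3.1 already defines the primary outcomes from baseline to postintervention and labels postintervention T1. This stands: deleting or keeping the 1-month visit leaves that window unchanged.

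A second reply is that section 2.3.1.8 defines attrition as participants withdrawn relative to those who consented, which does not depend on attendance at a visit. This helps only in part, because no date is given up to which withdrawals are counted.

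A reader might also infer more from the waitlist design: that controls will have had TSR by one month, so that the comparison there is no longer randomised, or that a three-time-point analysis would dilute the effect. The documents do not support this. They do not say when controls are offered TSR, and a condensed article may leave that to the full protocol. Sessions take about three weeks (section 2.2), so controls who started straight after T1 could finish within the month, while controls who started after the visit would still be untreated. Even with crossover, the arms compared as allocated remain a randomised comparison, and only its meaning changes, to immediate versus delayed TSR. Dilution would also require the third visit to enter the model, which section 2.4 does not state.

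**Conclusion.** The contradiction is real and visible within the article. One sentence places six scales at a 1-month visit, and Table 1 and the six scale sections place none there. This is an internal inconsistency that should be corrected before data collection, because it changes what is collected (up to 100 assessments) and leaves open the visit to which the 70% retention cut-off applies. The effect on Stop-Go depends on retention that is not yet known, so the figures above show when the choice of visit would matter and do not predict that it will.

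The point does not extend to the primary window, nor to a claim that the 1-month comparison is invalid. The missing T1 entry for the OSSS-3 is more serious in itself, since change in social support is a primary outcome. It is a separate matter, but the same edit to the table should correct it.

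**What to change.** Reconcile the opening of section 2.3.1 with the six scale sections and Table 1.

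- **If the visit is kept:** add a t2 column to Table 1 marking each scale to be collected there, and bring the scale sections into line. Correct the t1 entries for the scales that section 2.3.1 places at T1, including the OSSS-3. Label the t2 between-arm contrast as secondary, compare the arms as randomised, and interpret it as immediate versus delayed TSR if controls have been offered the sessions by then. Reporting the TSR arm alone at t2 would discard randomised data.
- **If the visit is not kept:** delete the reference to a 1-month follow-up from section 2.3.1. The t1 entries still need the same correction.
- **In either case:** state in section 2.4 the visit at which Stop-Go retention is counted, for example T1 as the primary endpoint visit.

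The cost is an amendment to text and table. It adds no visit beyond those that section 2.3.1 already promises.
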